### Outcome measures

Table 1 and 2 provide an overview of the measures at various time points. Participants of both groups are evaluated using a series of measures as mentioned below. The participants of the VRET group will undergo HR monitoring in real time, assessed for subjective discomfort/distress and evaluated for VR experience at T1 during the intervention as depicted in Table 1 and 2.

**Table 1 Tab1:** Showing overview of measures at different time periods

		Measurements						
		Primary outcome				Secondary outcomes (Only with VRET)		
		State anxiety (VAS-A)	Trait anxiety (MDAS)	Dental Fear Survey(DFS)	Behavioral test	Physiological parameter (HR)	Subjective Unit of Distress Scale (SUDS)	VR experience
Baseline (T0)	Screening interview	X	X	X	-	-	-	-
Intervention (T1)	Preoperative interview	X	X	X	X	-	-	-
	VRET^a^ session or IP^b^	-	-	-	-	X	X	X
	Postoperative interview	X	X	X	X	-	-	-
Follow-up (T2,T3)	E mail	X	X	X	-	-	-	-
Follow-up (T4)	E mail	X	X	X	-	-	-	-

Note: ‘X’ Indicates timing of measurement of the outcome measures

^a^VRET: Virtual Reality Exposure Therapy

^b^IP: Informational Pamphlet

**Table 2 Tab2:** Showing measures during VRET session

Measures		VRET session																											
		Baseline phase (10 min)	Training phase (2 min)	Experimental phase(Sessions repeated p,q,r,s,t times until SUDS score ≤2)																									Immediate Post-therapy phase (10 min)
				Scenario #1 (Idle)					Scenario #2 (Mirror)					Scenario #3 (Syringe)					Scenario #4 (Drill with no sound)					Scenario #5 (Drill with sound)					
1	Number of exposures			1	2	3	4	p	1	2	3	4	q	1	2	3	4	r	1	2	3	4	s	1	2	3	4	t	X
2	Subjective measure(SUDS)			X	X	X	X	X	X	X	X	X	X	X	X	X	X	X	X	X	X	X	X	X	X	X	X	X	X
3	Subjective measure(Presence)			X	-	-	-	-	X	-	-	-	-	X	-	-	-	-	X	-	-	-	-	X	-	-	-	-	X
4	Subjective measure(Realism)			X	-	-	-	-	X	-	-	-	-	X	-	-	-	-	X	-	-	-	-	X	-	-	-	-	X
5	Subjective measure(Nausea)			X	-	-	-	-	X	-	-	-	-	X	-	-	-	-	X	-	-	-	-	X	-	-	-	-	X
7	Objective measure(HR)	X	X	X	X	X	X	X	X	X	X	X	X	X	X	X	X	X	X	X	X	X	X	X	X	X	X	X	X

Note: ‘X’ Indicates timing of measurement of the outcome measures

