#### Treatment room configuration

The waiting and VR treatment area will be shaped, using cues usually present in these areas. For VRET, a simulated dental environment will be created, with a dental chair, overhead light, dental instruments and to enhance immersion characteristic dental clinic-related smell (drops of oil of cloves on cotton wool) will be introduced. The room temperature will be maintained at 21 °C.

The treatment room where the study will be conducted will be equipped with:Two networked computers and a HMD as described above.Oculus positional tracking camera mounted on a tri-pod: To track the head movements in real-time.Logitech C-920C webcam mounted on a tri-pod: To record the video for future validations and evaluate the participant’s body response during VRET.YOGA Mini Tie Clip Condenser Microphone: To record the voice of the participants during VRET, It is synchronized with the webcam.MIO LINK HR wrist band: To record the real-time HR of the participants during therapy.SUUNTO movestick mini: For wireless transfer of HR data from the wrist band to the simulator PC.PHILIPS wireless portable speaker BT100B/37: To produce characteristic dental drill sound.

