##### Experimental phase

In this phase, participants are exposed to five different VR scenarios (Idle, Mirror, Syringe, Drill with no sound, Drill with sound). The duration of each exposure will be 35 seconds. The interactive part of the simulated dental environment will be controlled by the researcher using the tool selection option on the UI window of the computer. The researcher will be able to control the playback of the VR scenarios.

VRET is conducted using a pre-determined hierarchy as follows:Scenario #1 (Idle). This shows a dental operatory with various instruments surrounding the patient’s chair and a virtual dentist sitting next to the patient’s right hand inside the 3D scene.Scenario #2 (Mirror). This shows the virtual dentist inspecting the oral cavity by picking the dentist’s mirror from the tray and approaching towards the patient’s oral cavity.Scenario #3 (Syringe). This shows the virtual dentist performing injection by picking the syringe from the tray and approaching towards the patient’s oral cavity.Scenario #4 (Drill with no sound). This shows the virtual dentist picking the drill and approaching towards the patient’s oral cavity with no sound of the drill.Scenario #5 (Drill with sound). This shows the virtual dentist picking the drill. The drill makes the characteristic dental drill sound when approaching towards the patient’s oral cavity.

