Participants will be exposed to the virtual dental scenarios in a gradual manner. To give the participants a gradual and optimal VRET, participants will be encouraged to rate their anxiety every 35 seconds following immersion with each VR scenario exposure by means of SUDS [39]. The general rule applied during exposure therapy is that the exposure is continued until the subjective score of the patient is reduced to less than 50 % [44].The VRET which we are planning to use in the current experiment has only a limited set of stimuli. Accordingly, we have decided to have a safe cut off of ≤2 SUDS scores before moving to the next VR scenario. This criterion was earlier applied in a similar study [17]. The exposures with scenario 1, 2, 3, 4 and 5 are repeated p,q,r,s and t times respectively until SUDS score of ≤2 is achieved. For instance, when participant reaches ≤2 SUDS with VR scenario of sitting idle on the dental chair then the next VR scenario of inspecting the oral cavity with a dental mirror is introduced. In subsequent sessions, the intensity of VR experiences will be progressively increased from a less threatening scenario to a more threatening scenario to make the simulation more realistic while focusing on areas of particular stress. For example, if a dental phobic participant report a fear of drills, the exposure is progressively increased from Scenario-1 (less fear evoking –‘Sitting in the dental chair’) to Scenario-5 (more fear evoking –‘Drill with sound’). To this end, situational cues that are simulated with VR scenarios are presented by the therapist in a well-controlled manner. During the simulated dental procedure participants will be asked to keep their mouth open similar to real dental experience from Scenario #2 (Examination with mirrors) through Scenario #5 (Drill with sound) and are advised to follow the instructions of the researcher, for example ‘to open their mouth really wide’. The added stimulus such as keeping the mouth open will be standardized and applied to all the participants. Participants will receive the therapy in one long session for 150 minutes with a 10-min break/s to avoid simulator sickness. If the participant’s SUDS rating has not decreased to 2 with any of the VR scenarios within 30 minutes of exposure the researcher will continue with the next VR scenario. The session will be video recorded for future validations and analysis of the subject’s body response during the VRET exposure.

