Only verbal guidance and exposure techniques will be used on the participants during VRET. There will be no relaxation or other CBT-based interventions during therapy. Participants will be instructed to become as involved as possible and focus on their most frightening stimuli of the particular part of the virtual environment (describing the situation, any strange sensations and their feelings). This will be done to avoid dissociation from the VR experience. During the simulated treatment, real-time recording of the psychophysiological parameters (HR) will be determined to obtain more ‘objective’ measures of the physiological state of the participants during therapy. The HR responses obtained with different cues (Idle, Mirror, Syringe, Drill with no sound and Drill with sound) in this phase will be compared with the baseline phase (No display) to study the HR variations. The subjective measures of presence, realism and nausea (cybersickness) are recorded following the 1^st^ exposure of each VR scenario as shown in Table 2.

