##### Immediate post-therapy phase

In this phase, the HR is recorded for 10 minutes and the participants are asked to fill out a series of self-reported measures as displayed in Table 2 and undergo the Behavioral Avoidance Test. The total number of VR exposures with each VR scenario will be summed up and recorded by the researcher. Also, the participants fill out the questionnaire on over-all presence, realism and nausea (cybersickness). After the VRET session, participants will remain in the waiting room for 15 min before leaving. This will be done in order to make sure that are no negative side effect of VRET *a posteriori*.

One week after treatment and at intervals of 3 and 6 months, the study participants will receive questionnaires that are used to assess the participants’ current dental anxiety scores and avoidance tendency (see Table 1) by email.

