Mean Baseline: Mean of HR during baseline phase of VRET session.

This will help us to compare and correlate between:Self-reported subjective scores (SUDS) and Objective scores (%HR during first VR exposure of each scenario) of anxiety. Determines the validity of HR (how well do self-report scores correlate with physiological measure of HR).Subjective measures of presence and the objective scores (%HR).Subjective measures of presence and realism.Objective scores (%HR) and subjective realism measures.Objective scores (%HR) and subjective cybersickness (nausea) measures.

The association between measures will be determined using the Pearson correlation coefficient.

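### Nausea is scored as cybersickness with no rating before the display is switched on, so nausea present on arrival cannot be separated from nausea arising during VR

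*Protocol article*

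**What the plan says.** Severity of nausea, labelled cybersickness, is listed under Secondary outcome measures as an 11-point verbal rating. Table 1 restricts the VR-experience measures to the VRET arm.

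- **During exposure.** The Experimental phase section states that "The subjective measures of presence, realism and nausea (cybersickness) are recorded following the" first exposure of each scenario. In Table 2 the row "Subjective measure(Nausea") is marked at exposure 1 of each scenario and dashed at every repeat.
- **After therapy.** The same row is marked in the last column, and the Immediate post-therapy phase section confirms it: "Also, the participants fill out the questionnaire on over-all presence, realism and nausea (cybersickness").
- **Before VR.** Table 2 marks heart rate in the 10-minute baseline phase and the 2-minute training phase but leaves nausea blank in both. The text on those two phases mentions only heart rate.
- **Session.** "The duration of each exposure will be 35 seconds", and a scenario is repeated until the distress score is 2 or less. If that is not reached "within 30 minutes of exposure the researcher will continue with the next VR scenario". Overall, "Participants will receive the therapy in one long session for 150 minutes with a 10-min break/s to avoid simulator sickness".
- **Analysis.** Heart rate is expressed as percentage change from the baseline phase, because resting levels differ between people. One planned correlation is between "Objective scores (%HR) and subjective cybersickness (nausea) measures", using first-exposure values.

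**The concern.** The label cybersickness assumes that VR is the cause, but the schedule has no reading from which a VR effect could be measured. Participants are phobic and lie supine in a dental chair, in a room where a "characteristic dental clinic-related smell (drops of oil of cloves on cotton wool) will be introduced". From scenario 2 they also hold their mouths open. Any of these could plausibly produce nausea, and some apply before any display is shown.

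Two uses of the data are affected. First, the description of how well VRET is tolerated mixes nausea brought into the session with nausea that arose in it. Second, the heart-rate correlation sets a within-person change against a raw level. Differences between participants in nausea on arrival then enter one side of the correlation and not the other.

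An analysis plan cannot repair this later, because the reference rating is never collected.

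**Working it through.** The plan states no figure to reproduce on this point. The check consists of reading the schedule and some simple arithmetic.

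**1. Count of ratings (Table 2, Experimental phase, Immediate post-therapy phase).**
- First exposures: 5 scenarios × 1 = 5.
- Post-therapy: 1.
- Total in the VRET arm: 5 + 1 = 6.
- Before the display is on: 0. In the pamphlet arm: 0.

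**2. VR time before the first rating.** Training is 2 min = 120 s and one exposure is 35 s. 120 + 35 = 155 s. The earliest rating is therefore not a pre-VR rating.

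**3. What can be identified.** As a simple additive description, write the nausea score at rating k as

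N(k) = A + V(k) + S(k),

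where A is nausea present on arrival, V(k) is nausea from the virtual display, and S(k) is nausea from other things that start during the scenarios, such as mouth opening or fear cues.
- *As planned:* N(k) contains A. The only available subtraction, N(k) − N(1), removes A but also removes whatever the first 155 s of VR produced.
- *With a headset-off rating N(0) = A:* N(k) − N(0) = V(k) + S(k). Arrival nausea is removed. V and S remain together.

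**4. The correlation.** The plan's formula is %HR = (mean HR in first exposure − mean baseline HR) / mean baseline HR × 100. Its partner is N(k), which still contains A. The two sides are on different footings.

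**5. How far build-up is captured.** Assume back-to-back exposures with no rating time.
- Exposures per scenario at the time limit: 30 × 60 / 35 = 51.4, so about 51, of which about 50 are repeats with no nausea rating of their own.
- Time from one scenario's first-exposure rating to the next scenario's: 35 s if one exposure suffices; at the limit, (1800 + 35) − 35 = 1800 s = 30 min. A break between scenarios lengthens this.
- Scenario 5, from its rating to the end of its exposures at the limit: 1800 − 35 = 1765 s, about 29 min, followed by the post-therapy rating.
- Order: scenarios run 1 to 5, so the rating at scenario 2 comes after all repeats of scenario 1 plus 35 s, and likewise through scenario 5. The post-therapy rating follows everything.

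Accumulated nausea is therefore sampled at intervals of between 35 s and about 30 min (longer with a break). What goes unrecorded is the course within a scenario and any peak that subsides before the next rating.

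The upper end cannot be typical: 5 × 30 = 150 min would fill the whole stated session and leave no time for breaks.

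**The case against.** The strongest case against is that the schedule is better than it looks.

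- **A reader might infer that nausea is rated only after the first 35 seconds and that build-up is missed.** The document does not support this. There is a post-therapy rating, and the ratings for scenarios 2 to 5 follow all repeats of the earlier scenarios. Without a break, an end-of-scenario rating would precede an existing one by only about 35 seconds for four of the five scenarios. A low proportion of exposures carrying a rating is also a poor index, because each later rating reflects earlier exposures.
- **A reader might infer that the operator has nothing to go on during the session.** Distress is asked at every exposure, participants are told to describe strange sensations, and they hold a panic button. These are not nausea scales, but they do provide information.
- **The first-exposure rule has a stated purpose,** which is to avoid order effects in the correlations. That justifies which values enter the correlations. It does not justify leaving out a baseline: heart rate is recorded throughout, and its correlations still use first exposures.
- **The reason for correcting heart rate need not carry over to a symptom scale.** This is fair as far as it goes. The need for a nausea reference rests instead on the label, which claims a cause.
- **A baseline rating does not fully solve attribution.** This is true. It leaves nausea from mouth opening and from fear cues in the scenarios.

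What survives is the missing pre-VR rating, together with a smaller point about peaks that fade.

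**Conclusion.** The point holds in a limited form. Six nausea ratings are planned in the VRET arm, none before the display is on and none in the pamphlet arm. Nausea present on arrival cannot be removed from the cybersickness outcome or from its correlation with heart rate.

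It would go too far to say that the ratings tell us nothing about VR: change across the six can still be described. It would also go too far to say that peak nausea is understated. That is a possibility, for example when symptoms ease over a break, and the document gives no data on it.

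The size of the distortion cannot be computed, because the document gives no figure for nausea on arrival. If arrival nausea is negligible, little is lost; without the rating, nobody will know. The interval figures assume back-to-back 35-second exposures. The primary outcomes, the randomisation and every between-group comparison are untouched. This is a cheap improvement to a secondary measure.

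**What to change.** **Main change.** In Table 2 and the Baseline phase section, add one 11-point nausea rating at the end of the 10-minute headset-off phase. This covers the same period as the heart-rate baseline; asking at its end avoids disturbing the resting recording. Report cybersickness as change from that rating, and use that change in the %HR correlation, keeping the first-exposure ratings as the post-baseline values.

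**Optional.** Add a rating after the last exposure of each scenario, or just before a break, when distress is already being asked. Report peak nausea descriptively.

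**Wording.** State that change from baseline still includes nausea from mouth opening and fear cues that begin during the scenarios, and do not claim full attribution to VR.

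**Cost.** Each rating takes a few seconds. Asking more often may prompt some symptom reports. The change concerns measurement only and leaves the exposure and break rules as they are.

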##### Immediate post-therapy phase

In this phase, the HR is recorded for 10 minutes and the participants are asked to fill out a series of self-reported measures as displayed in Table 2 and undergo the Behavioral Avoidance Test. The total number of VR exposures with each VR scenario will be summed up and recorded by the researcher. Also, the participants fill out the questionnaire on over-all presence, realism and nausea (cybersickness). After the VRET session, participants will remain in the waiting room for 15 min before leaving. This will be done in order to make sure that are no negative side effect of VRET *a posteriori*.

One week after treatment and at intervals of 3 and 6 months, the study participants will receive questionnaires that are used to assess the participants’ current dental anxiety scores and avoidance tendency (see Table 1) by email.

### Informational pamphlet control group (IP)

Participants in the IP group will be given three pages of information based on that of a dental website company, and of a fact sheet about dental anxiety from the Academy of General Dentistry [45]. The pamphlet will contain details about the standards of care such as patient comfort, description of dental procedures and postoperative pain management. Participants will be seated in the same area where they completed the screening and are given time to review the pamphlet in detail. Also, an opportunity is given to the participants to ask the researcher information about dental phobia. The study participants will receive a total of 5 assessments, T0, T1, T2, T3 and T4 similar to VRET intervention group.

Following interventions, the participants of both the groups are told that if they have any question/s about their condition, they can call a telephone helpline that facilitates patient access to information and address any questions they might have (between 08:00 to 17:00 from Monday to Friday).

## Sample size

Since the approach of the study is novel, there is scanty comparable research available to use for a sample size calculation. We used the difference between two independent means’ for sample estimation (independent-samples t-test). In a previous study [46] the response within each subject group was normally distributed with standard deviation (MDAS) 4.22. If the true difference in the experimental and control means (MDAS) is 6, we will need to study 12 experimental subjects and 12 control subjects to be able to reject the null hypothesis that the population means of the experimental and control groups are equal with probability (power) 0.9. The Type I error probability associated with this test of this null hypothesis is 0.05. Since drop-outs are unavoidable when collecting follow-up data, the sample number needs to be adjusted for the estimated drop-out rate. We are estimating a drop-out rate of 15 % in this study. Adjusting the sample for 15 % drop-out and 10 % for VR crash results in sample of 30 participants (15 experimental and 15 control participants).

## Data analysis

The analyses will be performed based on the Consolidated Standards of Reporting Trials (CONSORT) statement regarding e-health [47]. An independent biostatistician will carry out the statistical analysis using SPSS 20.0.The recorded data will be labelled so that the biostatistician will not be able to distinguish between the two groups. All data will be analyzed using an intention-to-treat analysis. We will also conduct a per protocol analyses. Descriptive statistics will be calculated, whereas discrete variables will be summarized by frequencies or proportions. Continuous variables will be reported as means and standard deviations or medians and range (depending on the measurement level of the variables). Data will be checked for differences at T0, T1, T2, T3 and T4 between the VRET and informational pamphlet group using independent samples t-test. Between-group changes at post treatment will be calculated by using a 2 (pre-treatment/post-treatment) × 2 (VRET/Informational pamphlet) repeated measures MANOVA. Post hoc comparisons will be applied if clarification of the main effects of the MANOVA is needed. Effect sizes between the groups will be calculated with Hedges’ g. Clinical significance change analyses as described by Jacobson and Truax [48] will be conducted to determine whether the changes from pre-test to post-test are clinically significant [48]. Missing data analysis will be performed and the reason for non-adherence will be registered.

The continuous monitoring of HR data will help us determine whether the physiological changes diminish following multiple exposures with each scenario (suggestive of habituation-Reliability of therapy).

To evaluate the correlation between subjective measures of VR experience (presence, realism, nausea) with objective measure of HR during each VR scenario, only the first exposure measures will be considered to eliminate the order effects as shown in Table 2.

Since the baseline physiology levels will vary widely between individuals, we will be determining the percentage change from baseline HR during the first exposure of each VR scenario for analyses rather than considering the absolute values. The percentage change of heart rate (%HR) will be calculated as follows:$$ \%\mathrm{H}\mathrm{R} = \left(\mathrm{MeanVR} - \mathrm{MeanBaseline}\right)/\mathrm{MeanBaseline}, \times 100 $$where,

MeanVR: Mean of HR during the VRET of 1^st^ exposure of each VR scenario, and

Mean Baseline: Mean of HR during baseline phase of VRET session.

This will help us to compare and correlate between:Self-reported subjective scores (SUDS) and Objective scores (%HR during first VR exposure of each scenario) of anxiety. Determines the validity of HR (how well do self-report scores correlate with physiological measure of HR).Subjective measures of presence and the objective scores (%HR).Subjective measures of presence and realism.Objective scores (%HR) and subjective realism measures.Objective scores (%HR) and subjective cybersickness (nausea) measures.

The association between measures will be determined using the Pearson correlation coefficient.

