A recent meta-analysis suggests VRET to be slightly, but significantly, more effective than IVET (in vivo exposure therapy) [27]. Although, VRET provides a powerful means of modifying affect, because of its immersive nature, it has not been tested yet as a therapy for dentally related anxiety or dental phobia. In an effort to answer this question, we will use VRET simulation software for the treatment of dental phobia and test its efficacy in the present study. The primary objective of the present study is to determine the efficacy of VRET versus an informational pamphlet control group in terms of dental trait and state anxiety reductions at 1 week, 3 months and 6 months follow-up among a sample of patients suffering from dental phobia. The secondary objectives are to determine (a) the real-time effect of VRET on the course of participant’s physiological response (HR) on exposure with a series of dentally related cues during therapy and (b) the relation between subjective (i.e., presence) and more objective (i.e., HR) measures during VRET. It is hypothesized that: (a) VRET would result in a significantly reduced level of dental trait anxiety [measured by MDAS (Modified Dental Anxiety Scale) and Dental Fear Survey (DFS)] and state anxiety [indexed by VAS-A (Visual Analogue Scale-Anxiety)] at 1 week, 3 months and 6 months follow-up compared to the informational pamphlet control group, (b) VRET would result in significantly higher reduced physiological arousal (i.e., HR) to dental anxious stimuli/cues relative to the baseline HR values following therapy, (c) VRET will demonstrate a positive correlation between subjective and objective measures of ‘presence’.

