## Discussion

The design of this randomized clinical trial offers pathways to address the efficacy of VRET in the treatment of long term trait dental anxiety. Therefore, we developed (KR, [name] and MB) a VRET device based on exposure therapy models and will be testing the efficacy of this intervention among people with dental phobia immediately after therapy, 1 week, 3 months and 6 months post therapy, and will be comparing with the results of an informational pamphlet intervention.

In recent years VRET has become a viable treatment alternative for in vivo exposure therapy as evidence based treatment for specific phobias with the advantage of allowing patients to face their fears in a controlled and thus safe, environment. Patients may not feel the anticipatory fear of getting hurt as they are aware that the VRET simulation is purely virtual and that these situations can be stopped, paused, restarted as well as repeated, whenever, for as many times as deemed necessary [10]. Accordingly, patients’ acceptance of VRET could be relatively high.

Another important advantage of the application of VRET for dental phobia is that it may not require specialized training and the entire exposure process can be completed by a computer in the safety and privacy of the practitioner’s office [10]. To this end, the study is a feasibility study. If proved successful, the VRET device can be rendered by any dental auxiliaries in a general dental practice which could make it a cost-effective solution. For example, because VR technology has applications in telemedicine, in which diagnosis and treatment can be administered from a distant site [49]. This may make VRET applicable in rural dental clinics, in which the therapist might not be available at long distances and the therapist views on a monitor with which the subject is interacting, and comment appropriately and therapeutically.

The strengths of our study design include randomized group allocation, use of validated standardized assessments and a long term follow-up. A limitation of the present study is the absence of IVET as gold standard control group. Yet, it is hoped that the findings of this study will provide evidence in support of the efficacy of VRET and therefore will be an important step in the treatment of dental phobia in the setting of the dental practice.

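### No primary scale or visit is made decisive: three primary scales are compared at three follow-up visits, while the stated alpha and power belong to one MDAS comparison at an unnamed visit

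*Protocol article*

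**What the plan says.** The primary objective in the Background compares the arms on "dental trait and state anxiety reductions at 1 week, 3 months and 6 months follow-up". Hypothesis (a), in the same paragraph, names MDAS and DFS for trait anxiety and VAS-A for state anxiety at those three visits. The Abstract and the section on primary outcome measures give the three scales equal rank. Table 1 and the outcome section also put the behavioural avoidance test under the primary heading. That test is done only before and after the intervention at T1 and appears in neither the primary objective nor hypothesis (a).

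The Data analysis section plans the comparison this way: "Data will be checked for differences at T0, T1, T2, T3 and T4 between the VRET and informational pamphlet group using independent samples t-test". It adds a 2 × 2 repeated measures MANOVA on pre- and post-treatment values. It does not say which scale, visit or test decides the primary question.

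The Sample size section works from a single scale: "If the true difference in the experimental and control means (MDAS) is 6", with "standard deviation (MDAS) 4.22", detected "with probability (power) 0.9". On alpha it says: "The Type I error probability associated with this test of this null hypothesis is 0.05". No visit is named.

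**The concern.** The primary hypothesis spans three scales and three follow-up visits, nine between-group comparisons in all, but the design figures describe one. A reader cannot tell from the protocol what result would make the trial positive. With about 12 evaluable participants per arm, the scales and visits may well disagree. If they do, the protocol gives no basis for saying which result counts, and the choice can be made once the results are known. A claim of efficacy resting on whichever comparison came out significant would not have the error control that the sample size calculation suggests.

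**Working it through.** **Inputs from the protocol.** MDAS difference 6, SD 4.22, alpha 0.05, power 0.9, 12 evaluable per arm (Sample size); three scales (primary outcome measures); three follow-up visits (primary objective). Sidedness is not stated. Two-sided is assumed because it reproduces the 12 per arm; a one-sided t-test would need 10.

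**Step 1: the plan's own figure.** Standard error = 4.22 × √(2/12) = 1.723. Noncentrality = 6 / 1.723 = 3.48. Critical t on 22 degrees of freedom = 2.074. Power = 0.914. The exact solution for power 0.9 is 11.45, rounded up to 12. The sample size is right for one MDAS t-test.

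**Step 2: number of comparisons.** 3 scales × 3 visits = 9. The T0 comparison is a baseline check and is left out. The behavioural test is also left out because it has no follow-up visit. Counting post-intervention T1 would give 12.

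**Step 3: if any one significant result counts, each test at two-sided 0.05.** The protocol states neither condition. 0.05 is used because it is the only alpha given.

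- Independent tests: 1 − 0.95^9 = 0.370. This is the upper bound for non-negative correlations. For 12 tests it is 1 − 0.95^12 = 0.460.
- Correlated tests: simulated t-tests under the global null, 12 per arm, 40,000 runs. The protocol gives no correlations, so these are assumptions. In the equal structure every pair of tests has correlation r. In the product structure r applies between scales and between visits, and pairs differing in both have r².

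| r | equal: any false positive | product: any false positive | favouring VRET (equal / product) |
|---|---|---|---|
| 0.5 | 0.27 | 0.30 | 0.14 / 0.15 |
| 0.6 | 0.24 | 0.27 | 0.12 / 0.14 |
| 0.7 | 0.21 | 0.23 | 0.10 / 0.11 |
| 0.8 | 0.17 | 0.19 | 0.09 / 0.10 |
| 0.9 | 0.12 | 0.14 | 0.06 / 0.07 |

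The last column counts only false results in favour of VRET. Under independence that figure is 1 − 0.975^9 = 0.204, and for a single two-sided test it is 0.025.

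**Step 4: if all nine must be significant.** The false-positive rate cannot exceed 0.05. The power cannot exceed the 0.914 of the single test. If every comparison had the same standardised effect as MDAS (an assumption) and the tests were independent, it would be 0.914^9 = 0.445. Positive correlation puts it between these two values.

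**Step 5: adjusting instead of choosing.** At 12 per arm, with the same difference and SD, Bonferroni over three tests (0.05/3) gives power 0.805 and over nine tests (0.05/9) gives 0.657. At 15 per arm, nine tests give 0.803. One named comparison keeps 0.914 at 12 per arm.

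**The case against.** Five points can be made for the protocol.

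- **The 0.05 is not a trial-wide claim.** It is tied to one test, and the Data analysis section gives no alpha for the t-tests. This stands. A reader might infer that the trial breaches an overall 5% it had promised; no such promise is made.
- **Hypothesis (a) is worded conjunctively.** It joins the scales and visits with *and*, so one significant result need not be enough. This also stands, and Step 3 is conditional for that reason. But the protocol does not adopt the all-significant rule either, and under that rule the stated power is not the power of the hypothesis.
- **Multiplicity methods may sit in an analysis plan that is not shown.** The absence of an adjustment is therefore not a fault here. What remains is in the protocol itself: several equal primary outcomes, and a sample size at full alpha for one of them.
- **The MANOVA may carry the main analysis.** It covers pre- to post-treatment only and is not described as a gate for the tests at T2 to T4, which are the visits in the primary objective.
- **The Discussion calls the work a feasibility study.** It also seeks evidence of efficacy, and the protocol states significance hypotheses and a power calculation.

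**Conclusion.** The concern holds in a conditional form. The primary question has no decisive scale or visit, and the sample size describes only one of nine comparisons. Until one is named, the trial's error rate and power for its primary hypothesis are undefined.

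The size depends on the rule. Under any-one-wins with 0.05 per test, the two-sided false-positive chance is at most 37%, about 17-30% at correlations of 0.5-0.8 and about 12-14% at 0.9. About half of those results would favour VRET. Under all-must-win there is no inflation, but a loss of power.

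Two stronger readings are not supported. A reader might conclude that the false-positive rate simply is several times 5%; that needs a success rule and a per-test alpha which the protocol does not give. A reader might also conclude that the sample size is wrong; it is correct for the single MDAS test.

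**What to change.** Before unblinding, and preferably before anyone who knows the allocation looks at outcome data, name MDAS at one visit as the single primary endpoint, tested at two-sided 0.05. MDAS is the scale the trial was sized on. Six months (T4) fits the Discussion's aim to "address the efficacy of VRET in the treatment of long term trait dental anxiety", but the Discussion also lists the earlier time points, and the sponsor may choose another visit. State that visit in the Sample size section too.

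Make the other MDAS visits, DFS, VAS-A and the behavioural test secondary. Test them with Holm or in a fixed sequence, or report them with confidence intervals only.

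The change is one of wording. The 12 evaluable per arm stand and no measurement is dropped. The cost is that the other scales and visits can no longer support a stand-alone claim of efficacy.
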